**Statistical tests and anticipated results**

*Missing data and data preparation*. We will implement strategies, such as the digital diary, follow-up phone-call reminders, and providing routine encouragement to continue exercise, to minimise missing data. Missing values will be replaced with group means. All statistical analyses will be performed on an intention-to-treat basis, using SPSS (version 24).

***Hypothesis 1.*** The two phases that each participant completes during the course of a cross-over trial are typically referred to as the two study periods.^49^ First, a preliminary test will be carried to rule out carryover effects and to test our study for validity.^50^ This will be performed by estimating the sum of the values measured during the two treatment periods for each participant and compared across the groups by using an independent samples *t*-test.^49^ Second, the within-participant differences in outcome variables between the study periods will be calculated using a two-sided Student’s unpaired *t*-test.^49, 50^ Treatment effects will be evaluated using an ANOVA with a mixed-effects model considering the longitudinal repeated measures, including the effects of time (T1, T2, and T3) within each study group and the interaction between time and intervention. Post hoc analysis using the Bonferroni correction will be performed. Hypothesis 1 will be supported if significant reductions in pain intensity and university absenteeism and a significant improvement in academic performance are reported following 12 weeks of HIAT compared with baseline measurements.

***Hypothesis 2.*** The mediation effects of increased progesterone levels on pain will be assessed using the Sobel test.^51^ A four-step model using linear regression will be tested. In Step 1, the regression coefficient between prostaglandin levels and pain (Path C) will be estimated. In Step 2, the regression coefficient between progesterone and prostaglandin levels (Path A) will be estimated. In Step 3, the regression coefficient between pain and prostaglandin levels, along with the mediator, progesterone levels (Path B), will be evaluated. Step 4: the Sobel test will be used to estimate the standard error of Path AB using the formula B^2^SA^2^ + A^2^SB^2^, where A and B are the regression coefficients of Paths A and B, respectively, and SA and SB are the standard errors of Paths A and B, respectively.^51^ The online Sobel test calculator (<http://quantpsy.org/sobel/sobel.htm>) will be used. Hypothesis 2 will be supported if the Sobel test indicates a significant (p < 0.05) mediation effect.

***Hypothesis 3***. The unadjusted mean costs and cost differences between HIAT and the usual care groups for total and disaggregated costs (intervention costs, healthcare utilisation costs, including healthcare services and medications utilised, and absenteeism costs) will be calculated.^48^ The seemingly unrelated regression (SUR) analyses will be used to estimate the total cost differences (ΔC) and effect differences (ΔE). The SUR analyses will be performed by adjusting for baseline demographic and health characteristics (such as pain intensity and menstrual-cycle length or the number of bleeding days) between groups.^48, 52^ The advantage of SUR is that two regression equations, one for ΔC and one for ΔE, are modelled simultaneously allowing possible correlations between cost and outcome differences to be accounted for.^48, 53^

The EQ-5D responses will be converted into utility scores to estimate the gain or loss of quality-adjusted life-years (QUALYs). The incremental cost-effectiveness ratio (ICER) will be calculated using the formula ICER = ΔC / ΔE. The advantage of this approach is that our confidence intervals do not rely on the usual normality assumption. Uncertainty surrounding the ICERs and the 95% confidence intervals around cost differences will be estimated using bias-corrected and accelerated bootstrapping with 5,000 replications.^48^ The cost-effectiveness of the intervention groups will be geographically represented using the cost-effectiveness plane (CE). The threshold (λ) for cost-effectiveness or the amount of money the country is willing to pay to gain one unit of effect (QALY) will be calculated.

Further, we will determine whether the intervention is cost-effective by utilising two other thresholds to test the robustness of our conclusion: (1) GDP per capita (in terms of purchasing-power parity), which is the threshold suggested by the World Health Organisation Commission for Macroeconomics and Health for an intervention to be ‘very cost-effective’;^54^ and (2) the country-specific thresholds published by Woods et al.,^55^ based on extrapolating the opportunity costs of healthcare spending in the United Kingdom. The cost-effectiveness acceptability curve (CEAC) will be derived based on the λ value. Using the CEAC, the cost-effective treatment options will be predicted based on the different λ levels. A secondary analysis will be performed from a healthcare perspective by excluding absenteeism costs.^48^ The robustness of the primary analysis will be tested using the following two sensitivity analyses: (1) repetition of the analysis including completed participants alone; and (2) excluding cost-outliers or data from participants with extremely high absenteeism costs.^48^ Hypothesis 3 will be supported if HIAT yields cost (direct and indirect) savings and results in lower healthcare utility compared with WLC receiving usual care at assessment T2.

***Qualitative data***: An independent transcription service will provide verbatim transcriptions of the focus groups. Participants’ anonymity will be maintained by replacing names with PINs. Transcripts will be compared with audio recordings to ensure data accuracy. Transcripts will be analysed using the process of thematic analysis, as described by Braun and Clarke.^56^ The PI will initially analyse the transcripts from each focus group individually and then compare emergent themes across all focus groups. The final set of themes will be confirmed as coherent and comprehensive by the collaborators.

1. Dawood MY. Primary dysmenorrhea: advances in pathogenesis and management. Obstetrics & Gynecology. 2006;108(2):428-41.

6. Dawood MY. Dysmenorrhea and prostaglandins. Gynecologic endocrinology: Springer; 1987. p. 405-21.

8. Kannan P, Cheung K-K, Lau BW-M. Does aerobic exercise induced-analgesia occur through hormone and inflammatory cytokine-mediated mechanisms in primary dysmenorrhea? Medical hypotheses. 2019;123:50-4.

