***Research design and recruitment.*** A mixed-methods study, including a cross-over RCT, and semi-structured focus groups, alongside economic evaluation, will be conducted. A Cross-over design will be adopted to minimize the effect of confounders and inter-individual variability (because each participant serves as their own control)^27^ and encourage participant enrolment in the trial.^28^ A mixed-methods approach will be considered because the combination of qualitative and quantitative methods can contribute to interdisciplinary and comprehensive research evidence.^29^ This trial will include: (1) a two-step screening phase for eligibility; (2) a baseline assessment (time-point [T1]); (3) 12 weeks of supervised treadmill training for the HIAT group; (4) post-treatment outcome assessments and economic evaluations at 12 weeks (T2); (5) a washout period for four weeks, followed by the cross-over of HIAT and WLC groups; (6) 12 weeks of supervised treadmill training for the WLC group; (7) outcome assessments at 28 weeks (T3); and (8) semi-structured focus groups at 32 weeks. Potential participants will be recruited via advertisements (study flyer) distributed at the Hong Kong Polytechnic University and the Education University of Hong Kong (please see upport letter) campuses and throughout the local community and by word-of-mouth.

***Sample size:*** G-Power analysis^30^ (3.1.9.2), set for an F-test (analysis of variance (ANOVA), was used to estimate the sample size required to reliably test the study hypotheses. We will enrol 130 participants (65 per group), allowing for a 30% attrition rate (the drop-out rate in our previous RCT^9^ with a seven-month follow-up was 20%–23%). For Hypothesis 1, the estimated sample size was 86 (43 per group). The power was set to 90%, the alpha level was 0.05, the drop-out rate was 30%, and effect-size was 0.60 (from our previous RCT^9^). For Hypothesis 2, based on estimated changes in progesterone levels from our pilot trial (***d*** = 0.36),^13^ the sample size required to detect differences in progesterone with 90% power at the 5% significance level is 100 (50 per group). Assuming a 30% drop-out rate, 130 participants (65 per group) would be required.

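### The model assigned to treatment effects is a time-by-group model with no specified HIAT contrast, and the plan does not say whether it or the period-difference t-test decides

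*Protocol*

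**What the plan says.** The protocol's section on research design and recruitment describes a two-sequence, two-period cross-over, chosen "because each participant serves as their own control". HIAT or wait-list control runs for 12 weeks to T2. Then comes "a washout period for four weeks, followed by the cross-over of HIAT and WLC groups", and the last outcome visit is "outcome assessments at 28 weeks (T3").

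Under Hypothesis 1, the section on statistical tests and anticipated results sets out these elements:

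- A carryover pre-test on each participant's sum over the two periods.
- A cross-over test: "the within-participant differences in outcome variables between the study periods will be calculated using a two-sided" unpaired t-test.
- A mixed-effects ANOVA that is to evaluate treatment effects, "including the effects of time (T1, T2, and T3) within each study group and the interaction between time and intervention".
- A follow-up step: "Post hoc analysis using the Bonferroni correction will be performed". The comparisons and their number are not given.
- A support rule: Hypothesis 1 holds if significant improvements "are reported following 12 weeks of HIAT compared with baseline measurements".

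The sample size calculation was "set for an F-test (analysis of variance (ANOVA"), with an effect size of 0.60 for Hypothesis 1. It gives neither the number of measurements nor the correlation between them.

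**The concern.** The sentence that claims the treatment effect points to a model laid out as for a parallel-group trial: time, group, and their interaction. In a cross-over the groups swap treatment between T2 and T3, so a group-by-time interaction is not itself a statement that HIAT beats control. The omnibus test can be significant because of any pattern of group differences over the three visits, including one against T1.

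The test that does answer the cross-over question stands one sentence earlier and is not named as decisive. The support rule refers to neither test, since it looks at change from baseline after HIAT. Three non-equivalent routes to a conclusion can disagree, and nothing written in advance says which one governs the treatment comparison. The plan also does not fix the one number a reader will want: the HIAT-minus-control difference with its interval.

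**Working it through.** **Inputs.** From the protocol: 65 per group, 30% attrition (65 × 0.7 = 45.5, taken as n = 45 completers per group), effect size d = 0.60 for Hypothesis 1, two-sided alpha 0.05. Assumed, because the protocol gives none: equal correlation rho of 0.3, 0.5 or 0.7 between visits, equal SDs (set to 1), d as a standardised between-person effect, and no carryover unless stated.

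**The plan's own figure.** The protocol states no power for either test. Its Hypothesis 1 sample size of 86 cannot be matched to either one, because the inputs a repeated-measures calculation needs are not stated. The check below therefore compares the two tests with each other.

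**What the interaction contains.** Expected changes from baseline at (T1, T2, T3) are (0, −d, 0) for HIAT first and (0, 0, −d) for wait-list first. The group differences are (0, −d, +d). Between visits they change by −d for T2−T1, by +d for T3−T1 and by +2d for T3−T2. The group main effect is expected to be 0 even if HIAT works fully. The cross-over effect is half of the T2-versus-T3 by group contrast, so it sits inside the interaction as one component of a 2-df test.

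**Noncentrality (lambda).**

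- Cross-over contrast, 1 df: (2d)² / [4(1 − rho)/n] = n·d²/(1 − rho).
- Group-by-time interaction, 2 df: (n/2)·(0 + d² + d²)/(1 − rho) = n·d²/(1 − rho), the same value.
- T1-to-T2 change between groups, 1 df: d² / [4(1 − rho)/n] = n·d²/[4(1 − rho)], one quarter of it.

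At n = 45, d = 0.60, rho = 0.5: 45 × 0.36 / 0.5 = 32.4 for the first two, and 32.4 / 4 = 8.1 for the third.

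**Power at n = 45 per group, d = 0.60** (noncentral F):

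| rho | lambda, first two tests | 2-df interaction | 1-df cross-over contrast | T1-to-T2 change, no multiplicity correction |
|---|---|---|---|---|
| 0.3 | 23.14 | 0.993 | 0.997 | 0.662 |
| 0.5 | 32.40 | above 0.99 | above 0.99 | 0.804 |
| 0.7 | 54.00 | above 0.99 | above 0.99 | 0.953 |

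The extra degree of freedom costs 0.997 − 0.993 = 0.004, or 0.4 points, at rho 0.3, and less at higher rho.

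**If carryover is complete.** Suppose the HIAT-first group keeps its full benefit at T3. The group differences become (0, −d, 0). The cross-over contrast then has lambda 8.1 and power 0.804 at rho 0.5. The interaction has (n/2)·(2/3)d²/(1 − rho) = 10.8 and power 0.839. The cross-over estimate becomes (0 − d)/2 = −d/2, half the true effect.

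**The case against.** The strongest case against is that little is missing. In a two-sequence, two-period design the treatment effect is the sequence-by-period interaction, so the stated model contains it, and one contrast line yields the estimate and its interval. The period-difference t-test is valid and, with complete data, equivalent to the model proposed below. The word including does not make the term list exhaustive, and contrasts are commonly left to a statistical analysis plan.

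Most of this stands, and it rules out several stronger readings that a reader might infer:

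- *That the plan has no cross-over analysis, or that the model cannot give a HIAT effect.* It has one, and the effect is recoverable; the plan only fails to ask for it.
- *That the interaction loses meaningful power.* At the Hypothesis 1 effect size it does not. The smaller d of 0.36 is the progesterone figure for Hypothesis 2, which is analysed by regression and the Sobel test, so it should not be used to size a loss here.
- *That the Bonferroni step has a known low power.* The protocol does not list the comparisons, so any such figure would rest on a set chosen by the reader.
- *That the model would miss a real effect if intervention means treatment received.* If no treatment main effect is fitted, the time-by-treatment term absorbs it. If one is fitted, it is itself the HIAT estimate.

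What does not stand is the appeal to detail left for later. The protocol itself names the terms and assigns treatment effects to this model, in the same paragraph as a different test, and ranks neither.

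**Conclusion.** The point holds as a defect of specification. Read literally, the analysis assigned to treatment effects is a 2-df group-by-time test that is not a directional HIAT-minus-control comparison. The contrast that would make it one is not requested, and the valid period-difference t-test is not declared decisive.

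The size is modest. The power cost of the omnibus test is under 1 point at d = 0.60 with 45 completers per group and rho between 0.3 and 0.7. It becomes material only if the effect is read from the T1-to-T2 comparison between groups, where power is 0.662 to 0.953 over the same range before any multiplicity correction. These figures rest on the assumed correlations, compound symmetry, equal SDs and no carryover. The lack of a deciding test does not depend on them. It should be corrected, but it does not invalidate the design.

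**What to change.** Name one deciding treatment-effect analysis for Hypothesis 1: a mixed model on the T2 and T3 values with fixed effects for treatment received, period and sequence, and a random participant effect. Report a single HIAT-minus-control estimate with 95% CI and its 1-df test. State that with complete data this is equivalent to the period-difference t-test already planned.

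Label the time-by-group interaction and the Bonferroni visit comparisons as supportive or descriptive. Tie the Hypothesis 1 support rule to the deciding contrast in place of change from baseline alone.

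The one downside is reliance on no carryover: with full carryover the estimate is halved, as shown above. Keep the between-group comparison at T2, which later carryover cannot affect, as a sensitivity analysis.

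The cost is rewording of one paragraph. No new data are needed, and the planned software fits the model.

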***Pilot trial***: We conducted a pilot trial to examine the effects of HIAT on plasma biomarkers that have been implicated in the pathophysiology of primary dysmenorrhea. The pilot trial findings indicated a trend towards increased progesterone levels (***d*** = 0.36) and decreased levels of prostaglandin F2 alpha (PGF2α) metabolites (***d*** = 0.35) in the HIAT group compared with those in the control group, which suggested that aerobic exercise may affect primary dysmenorrhea pain through effects on these mediators.^8, 13^

Because our research has supported the beneficial effects of HIAT, and a recent pilot study suggested a link between HIAT and progesterone and prostaglandin levels, the proposed randomised, controlled cross-over trial will test the following three hypotheses: (1) HIAT for 12 weeks will lead to significant reductions in pain intensity and absenteeism and improve academic performance compared to baseline levels; (2) pain improvements will be mediated by increased progesterone levels, resulting in decreased PGF2α levels; (3) HIAT will display superior cost-effectiveness compared with usual care (Wait-list control [WLC]) for primary dysmenorrhea treatment.

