**Scientific premises for the study hypotheses**

*Hypothesis 1****.*** Previous research has shown that primary dysmenorrhea-associated pain intensity can be reduced by 30 minutes of HIAT, performed three days a week at 70%–85% of the age-adjusted maximum heart rate (MHR).^10, 14^ The RCT performed by the PI of the current proposal showed that this amount of exercise had positive and beneficial effects on pain and QoL in women with primary dysmenorrhea.^9^ Our RCT demonstrated statistically significant improvements in primary dysmenorrhea-associated pain and the mental component of QoL, and the results surpassed the threshold for clinical significance.^9^ Therefore, we hypothesise that HIAT for 12 weeks will lead to significant reductions in pain intensity and absenteeism and improve academic performance compared to baseline values.

*Hypothesis 2.* The hormones that dominate menstrual cycles are affected by exercise. Several studies have found that exercise increases progesterone levels during the luteal phase.^15-18^ High-intensity exercise has been found to induce alterations in circulating progesterone levels in both young and premenopausal women.^19, 20^ Furthermore, exercise has been associated with a reduced prevalence of primary dysmenorrhea in several studies.^14, 21-24^ Our preliminary studies^9, 10^ also found that women who participated in HIAT reported more pain relief than no-treatment controls. Because high-intensity aerobic exercise can influence both progesterone levels and analgesic effects in dysmenorrhea, we propose that improvements in pain are mediated by increased progesterone levels and the resultant decrease in PGF2α levels. Our pilot data also support this hypothesis.

*Hypothesis 3*. An economic evaluation, from the HK societal and healthcare perspective, is necessary due to cultural diversity, economic dynamics, and country-specific healthcare policies.^25, 26^ Such an evaluation will assist in decision-making regarding cost-effective treatment options for the HK population. Given the evidence supporting the beneficial effects of HIAT from our preliminary studies and the findings of our recent pilot study, which suggested a link between HIAT and progesterone levels, we hypothesise that HIAT will be superior to WLC (receiving usual care), in terms of cost-effectiveness.

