***Participants:*** Eligibility criteria are consistent with the guidelines for the diagnosis of primary dysmenorrhea established by the Society of Obstetrics and Gynecologists of Canada.^31^ Inclusion criteria include: (1) 18–24 years old; (2) non-pregnant; (3) having regular menstrual cycles with cycle lengths between 24 and 30 days; (4) experiencing an average menstrual pain intensity equal to or greater than 5 on a 0–10 Numerical Rating Scale (NRS); and (5) scoring low (< 600 metabolic equivalent tasks [MET]/week) on the short-form of the International Physical Activity Questionnaire (IPAQ).^32^ Exclusion criteria include: (1) the use oral contraceptive pills, hormonal therapy, or intrauterine devices; (2) the use of over-the-counter analgesics during menstruation to treat dysmenorrhea-associated pain, experience no pain relief with those analgesics and (3) participation in any formal exercise programme.

***Randomisation and blinding.*** An individual who is not involved in the study will develop a randomisation schedule (computer-generated) and prepare 130 sealed, opaque envelopes for allocation concealment. The sealed opaque envelopes will contain the group name (HIAT or WLC) and personal identification number (PIN). Following the baseline assessment, participants will select an envelope containing the details of their treatment allocation. The nature of the intervention is such that neither the participants nor the therapist can be blinded to the treatment allocation. A blinded examiner (research assistant [RA]) will assess study outcomes and collect saliva for the estimation of primary and secondary mediators. The RA will be trained to perform outcome assessments and saliva collection procedures by the PI and collaborators, respectively, during a full-day training workshop. Enzyme-linked immunosorbent assays (ELISAs) will be performed by a blinded research postgraduate student (RPg) on the saliva samples, which will be labelled using the PINs by Student Assistant #2. The student assistant will enter raw data into an Excel spreadsheet for analysis. Data analysis will be conducted in a blinded manner, using coded groups (Group A and Group B). The group code will be revealed only after the analyses have been completed.

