***Procedure:*** Potential participants will undergo a two-step screening process. The first step will be conducted via telephone interview, using an eligibility checklist. Potentially eligible women will then be invited to an in-person screening session on the first day of their next menstrual period. During this session, women will complete the screening questionnaire and IPAQ to determine eligibility, assess baseline physical-activity levels, and obtain written informed consent and anthropometric measurements. Baseline assessments of primary and secondary outcomes and the costs and absenteeism data associated with each individual’s previous three menstrual cycles will be performed, and saliva samples will be collected. Participants will then be randomised into HIAT or WLC groups. Participants in the HIAT group will receive supervised treadmill training for the first 12 weeks of the trial. To minimise carryover effects, a four-week washout period will be observed for all study participants before cross-over. During the washout period, the HIAT group will discontinue exercise, and both groups will continue to manage pain as usual (i.e. with analgesics). After the four-week washout period, the cross-over period will begin during Week 16, and the participants initially randomised to the WLC group will receive the HIAT regimen from Weeks 14–28. Participants initially randomized to HIAT group will be instructed not to engage in exercise during the remainder of the study period (i.e. Weeks 14-28). Participants will be permitted to use analgesics for menstrual pain as needed throughout the study and will be instructed to record the dose and number of pills consumed in an electronic diary. As a diagnosis of primary dysmenorrhea can be confirmed by collecting detailed history;^33, 34^ a pelvic examination/ ultrasound will not be conducted.

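### Hypothesis 1 is declared supported on change from baseline after HIAT; the randomised comparison with the wait-list control is planned but is not a condition of the rule

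*Protocol*

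**What the plan says.** Three places in the protocol word Hypothesis 1 the same way.

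- Background of Research, list of hypotheses: "HIAT for 12 weeks will lead to significant reductions in pain intensity and absenteeism and improve academic performance compared to baseline levels".
- Scientific premises, Hypothesis 1: "significant reductions in pain intensity and absenteeism and improve academic performance compared to baseline values".
- Statistical tests and anticipated results, Hypothesis 1: support requires significant falls in pain and absenteeism and a "significant improvement in academic performance are reported following 12 weeks of HIAT compared with baseline measurements".

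The last of these paragraphs also plans two analyses that use the randomised groups. In the first, "the within-participant differences in outcome variables between the study periods will be calculated using a two-sided" unpaired t-test. The second is a mixed-effects ANOVA, "including the effects of time (T1, T2, and T3) within each study group and the interaction between time and intervention". The sentence that states when the hypothesis is supported refers to neither. The rule for Hypothesis 3, by contrast, names WLC at T2 as its comparator.

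Three features of the design bear on change from baseline:

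- **Entry.** Women qualify by "experiencing an average menstrual pain intensity equal to or greater than 5" on the 0-10 NRS (Participants).
- **Baseline.** It is taken at the in-person screening session, where absenteeism is collected for the "previous three menstrual cycles will be performed, and saliva samples will be collected" (Procedure). Later absenteeism comes from a prospective electronic diary (Outcome measures).
- **Assessments.** Only T1, T2 (12 weeks) and T3 (28 weeks) are listed (Research design).

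**The concern.** A before-after rule credits HIAT with anything that would have changed anyway. In this trial the possible sources are regression to the mean in pain, the passage of time or season, and a likely change in how absenteeism is recorded. Women in the WLC group finish HIAT at week 28, and the only listed baseline is T1, so their change from baseline spans 28 weeks. The wait-list control would share such drift, and a contrast with it removes the shared part. Under the rule as written, both between-treatment tests could be null and Hypothesis 1 would still be reported as supported. The protocol itself fixes this criterion, so it is not a detail left to a later analysis plan.

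**Working it through.** The plan gives no error rate for its rule, so there is no figure to reproduce. The check asks how often the rule is met when the HIAT effect is zero.

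**Inputs from the protocol.** There are 65 women per group, 130 in all, with 30% attrition: 65 × 0.7 = 45.5, about 45 in one group, and 130 × 0.7 = 91 if both HIAT periods are pooled. Tests are two-sided at 0.05, so 2.5% in the favourable direction. The pain cut-off is 5. Hypothesis 1 effect size: "The power was set to 90%, the alpha level was 0.05, the drop-out rate was 30%, and effect-size was 0.60".

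**Inputs assumed, because the protocol gives none.** Pain before selection is normal with SD 2 and mean μ of 5 to 6. The repeat correlation r is 0.5 to 0.8. Shared drift is 0 to 0.5 SD. The inter-outcome correlation is 0.3. The normal model ignores the 0-10 bounds of the scale.

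**Step 1: pain alone, if the entry score is also the baseline score.** Expected fall = (1 − r) × SD × φ(z)/(1 − Φ(z)), with z = (5 − μ)/SD.

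- μ = 5: z = 0, ratio 0.798, so the fall is 1.596 × (1 − r) = 0.80, 0.48 and 0.32 points at r = 0.5, 0.7 and 0.8.
- μ = 6: z = −0.5, ratio 0.509, so the fall is 1.018 × (1 − r) = 0.51, 0.31 and 0.20 points.

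Simulated chance of a significant favourable paired t-test:

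| n | μ | r = 0.5 | r = 0.7 | r = 0.8 |
|---|---|---|---|---|
| 45 | 5 | 82% | 57% | 40% |
| 45 | 6 | 43% | 27% | 19% |
| 91 | 5 | 98.7% | 87% | 69% |
| 91 | 6 | 73% | 49% | 34% |

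**Step 2: pain alone, if entry and baseline are separate readings of equal reliability.** The regression then happens before baseline, and the chance returns to about 2.5%.

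**Step 3: pain alone, general drift δ in SD units.** The paired test has noncentrality δ√n / √(2(1 − r)). With r = 0.5 the divisor is 1. For n = 65 and δ = 0.3 it is 0.3 × 8.06 = 2.42, which gives 66%. At δ = 0, 0.2 and 0.5 the chance is 2.5%, 36% and 98%.

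**Step 4: the full rule, all three outcomes significant.** This is a simulation with n = 65, r = 0.5 and the same drift in each outcome. The comparison is a between-group test of T1-T2 change, standing in for the cross-over contrast.

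| Shared drift | Rule as written | Between-treatment rule |
|---|---|---|
| 0 | about 0% | under 0.1% |
| 0.2 SD | 9% to 10% | under 0.1% |
| 0.3 SD | 37% | under 0.1% |
| 0.5 SD | 94% | under 0.1% |

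For pain alone, the between-group test stays near 2.5% at every drift. If the only source of drift is selection on pain, reaching the other two outcomes through the 0.3 correlation, false support under the full rule is about 0.3% to 7%.

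**Step 5: can a control-based rule be afforded?** Reading the stated 0.60 as a standardised mean difference (the protocol does not name the metric), power per outcome = Φ(0.60 × √(n/2) − 1.96). With 65 per group this is Φ(3.42 − 1.96) = 92.8%, and with 45 per group Φ(2.85 − 1.96) = 81.2%. This takes no credit for the cross-over or for baseline adjustment. Power for all three outcomes together would be lower.

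**The case against.** The best defence is that the control is in the analysis. The protocol says treatment effects will be evaluated by a model with a time-by-intervention interaction, and it plans the standard cross-over t-test; both would be reported. That stands, so a reader should not infer that randomisation plays no part in the analysis. The defect is confined to the decision rule.

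Four further inferences are tempting and not supported:

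- **That the primary claim carries a false-positive rate of 19% to 99%.** Those figures are for pain alone. The rule joins three outcomes with *and*, so it is conservative when there is no drift.
- **That regression to the mean is certain.** Entry uses average menstrual pain, with screening that starts by telephone; the outcome is average pain over the last 24 hours during menstruation. The protocol does not say that one reading serves both purposes.
- **That a between-treatment rule cures expectation bias.** The wait-list participants are unblinded and untreated, so the contrast carries that bias too.
- **That the mixed ANOVA fails because the groups swap treatment between T2 and T3.** If intervention means treatment received, the model allows for the swap. If it means randomised group, the interaction still contains the T1-T2 contrast. The wording is ambiguous, and coding is ordinary analysis-plan detail.

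The direction of any shift from the change in absenteeism recording is also unknown.

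**Conclusion.** The point holds for the decision rule. All three statements of Hypothesis 1 name baseline as the comparator, and no between-treatment result is required for support. This conclusion needs no number: the rule cannot attribute an improvement to HIAT. How often it would mislead depends on assumed drift, which the protocol does not let one estimate. The risk is negligible with no drift, a few per cent if the only source is selection on pain, and substantial (about 37% at 0.3 SD, 94% at 0.5 SD) if all three outcomes drift together. Because the rule governs the primary claim and correcting it needs no new data, it should be changed.

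**What to change.** Reword Hypothesis 1 in Background of Research, in Scientific premises and in Statistical tests: it is supported if the HIAT-minus-WLC difference is significant, in favour of HIAT, for pain intensity, absenteeism and academic performance, all three as now.

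Estimate the difference from the planned cross-over analysis. This can be the unpaired t-test on within-participant period differences, or a mixed model with fixed treatment, period and sequence and a random participant effect. The two are equivalent only with complete data; as 30% attrition is allowed for, name one as primary. Add the T2 comparison of the randomised groups, adjusted for T1, as a sensitivity analysis. Report change from baseline descriptively.

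The cost is wording only; the data and the between-treatment test are already planned. The downside is that the between-treatment effect will probably be smaller than the before-after change, so the hypothesis becomes harder to support. Expectation bias in the self-reported outcomes remains and should be stated as a limitation.
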